### Plans to give access to the full protocol, participant-level data and statistical code {31c}

Upon publication of primary results, we will make the final study protocol, anonymized participant-level dataset, and statistical code used for the analysis publicly available on the Open Science Framework (OSF).

[https://osf.io/46qhb/?view_only=82598d792f304ee692fd636c94d5e7eb].

## Oversight and monitoring

### Composition of the coordinating center and trial steering committee {5d}

The trial will be coordinated from Uppsala University, Sweden, which will handle overall study management, including ensuring ethics compliance, data oversight, and reporting. The Trial Steering Committee (TSC), comprising all co-authors, will supervise the study, convening regularly to monitor progress and resolve emerging issues.

### Composition of the data monitoring committee, its role and reporting structure {21a}

Due to the low-risk nature of the interventions and their prior use in similar settings without evidence of serious harm, a separate data monitoring committee will not be established. Oversight of trial conduct and participant safety will instead be provided by the Trial Steering Committee and the relevant ethics committees.

### Adverse event reporting and harms {22}

SH+ is a brief, low-intensity stress-management intervention and prior studies have not indicated intervention-related harms as a common concern. Nonetheless, clinically significant deterioration or safeguarding concerns may be identified during sessions or assessments. Adverse events will be captured non-systematically through spontaneous reporting and facilitator/staff observation. Any adverse event will be reported to the Trial Steering Committee within 24 h. The Trial Steering Committee will evaluate severity and assess whether the event is related to the study intervention. Serious adverse events will be reported to the relevant ethics committees for review. In trial reporting, adverse events identified through spontaneous reporting will be summarized descriptively by trial arm, consistent with CONSORT-SPI 2018 [58] and guided by CONSORT Harms 2022 [59] as appropriate.

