#### Enhanced Usual Care (EUC)

All enrolled participants (mothers) will receive EUC, which consists of a single 15-min psychoeducation session delivered individually by a trained research assistant under the supervision of a clinical psychologist from our implementation partner, *vivo international*. The session is guided by a predetermined script, focusing on the locally salient concept of “overthinking” [22] and introducing brief, practical self-management techniques. Following the session, participants are provided with standardized information about available mental health resources within Rhino Refugee Settlement, including services provided by UNHCR partner organizations and a network of community-based health workers trained to offer basic psychosocial support. EUC is delivered to all participants after the baseline assessment; for those in the intervention arm, it precedes the start of SH+.

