#### Self-Help Plus (SH+)

Participants in the intervention arm will additionally receive Self-Help Plus (SH+), a World Health Organization (WHO) brief, low-intensity intervention designed for stress management in communities affected by adversity [12, 13]. SH+ is based on Acceptance and Commitment Therapy (ACT) and is delivered in a group-based format (up to 30 participants) over five weekly sessions, each lasting approximately 2 h.

The core content is delivered via pre-recorded audio material (using the Juba Arabic adaptation), which is integrated with individual exercises and guided group discussions. Participants also receive an illustrated, low-literacy self-help book to review strategies and practice skills between sessions. This multimedia format, guided by a facilitator manual, is designed to enhance fidelity and minimize extensive training demands, making it suitable for scalable delivery in low-resource settings.

Sessions are co-facilitated by pairs of trained local lay-providers who reside in the settlement, have completed at least secondary education, and are proficient in both Juba Arabic and English. The training and supervision of these facilitators are led by experienced mental health specialists from *vivo international Uganda*. These specialists first completed a comprehensive Training of Trainers (ToT) conducted by the research team using WHO materials and guidelines. The ToT equipped them to deliver the SH+ training, conduct fidelity assessments, provide supervision, and manage referral pathways. Following this, the *vivo* specialists provide the facilitators with 5 days of specialized SH+ training and a 3-day supervised, hands-on pilot with test participants. Ongoing weekly supervision from these specialists includes a review of session checklists, feedback on delivery, and guidance on managing group dynamics to ensure fidelity to the SH+ model.

SH+ materials have been professionally translated and culturally adapted into Juba Arabic following established best practices [26], and are publicly available on the WHO website [27].

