### Participant timeline {13}

The SPIRIT participant flow diagram is shown in Fig. 2. Baseline data will be collected immediately after participants complete screening, provide informed consent, and are enrolled in the study. All participants will then receive a single session of Enhanced Usual Care (EUC) before randomization. Those assigned to the intervention arm will then participate in the Self-Help Plus (SH+) program, which consists of five weekly group sessions. Follow-up assessments will be conducted at 3 and 12 months post-intervention.

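### The by-arm adverse-event summary rests on capture that is more intensive in the SH+ arm, and its wording leaves unclear whether observed events are counted

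*Protocol article*

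**What the plan says.** The section on adverse events and harms {22} fixes both how harms are found and how they are shown.

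- **Capture:** "Adverse events will be captured non-systematically through spontaneous reporting and facilitator/staff observation".
- **Setting:** "clinically significant deterioration or safeguarding concerns may be identified during sessions or assessments".
- **Reporting:** "adverse events identified through spontaneous reporting will be summarized descriptively by trial arm".

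The intervention sections show who is there to observe.

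- **SH+:** the programme runs "over five weekly sessions, each lasting approximately 2 h", and "Sessions are co-facilitated by pairs of trained local lay-providers who reside in the settlement".
- **EUC:** this is "a single 15-min psychoeducation session delivered individually by a trained research assistant", and its timing is fixed in the participant timeline {13}: "All participants will then receive a single session of Enhanced Usual Care (EUC) before randomization".
- **Both arms:** "Follow-up assessments will be conducted at 3 and 12 months post-intervention". The retention section {18b} adds three short administrative calls to keep contact details current.

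No harms enquiry put in the same form to both arms is described.

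**The concern.** One of the named capture routes, observation by facilitators, operates in one arm only. SH+ mothers also have more occasions to volunteer a problem to someone in the study. A table by arm built on such capture mixes the frequency of events with the chance that they are noticed. At equal true risk it would tend to show more events under SH+, and a reader could take that for harm caused by the intervention. Conversely, a true excess in EUC could be hidden.

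This matters because mothers are selected for distress (K6 of 5 or more) and the article itself expects that deterioration may be seen. There is no separate data monitoring committee, and relatedness is judged by a steering committee made up of the co-authors. A comparable control-arm rate is what would allow events seen under SH+ to be interpreted. An analysis plan cannot repair this later, since it cannot recover events that nobody asked about.

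**Working it through.** The article gives no adverse-event rate, so there is no figure of its own to reproduce.

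**Step 1. Scheduled study contact after allocation**

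| Contact | SH+ | EUC only | Source |
|---|---|---|---|
| Facilitated sessions | 5 × 2 h = about 10 h | 0 h | Self-Help Plus (SH+) |
| EUC session | none (before randomization) | none (before randomization) | Participant timeline {13} |
| Follow-up assessments | T1, T2 | T1, T2 | Participant timeline {13} |
| Administrative calls | 3 | 3 | Retention {18b} |

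The facilitated sessions are the only scheduled contact that differs.

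**Step 2. What unequal detection does at equal true risk**

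Let p be the true risk in both arms, s the probability that an event is detected by routes shared by both arms, and f the additional, independent probability of detection through SH+ sessions. With 720 dyads randomized 1:1 there are 360 mothers per arm.

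- Expected recorded events in EUC = 360 × p × s
- Expected recorded events in SH+ = 360 × p × [1 − (1 − s)(1 − f)]
- Ratio SH+ to EUC = [1 − (1 − s)(1 − f)] / s, in which p cancels

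The values of p, s and f are assumptions.

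| Ratio | f = 0.1 | f = 0.3 | f = 0.5 |
|---|---|---|---|
| s = 0.2 | 1.40 | 2.20 | 3.00 |
| s = 0.4 | 1.15 | 1.45 | 1.75 |
| s = 0.6 | 1.07 | 1.20 | 1.33 |

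Lowest case: [1 − 0.4 × 0.9] / 0.6 = 0.64 / 0.6 = 1.07. Highest case: [1 − 0.8 × 0.5] / 0.2 = 0.60 / 0.2 = 3.0.

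Middle case in counts, with p = 10%: EUC 360 × 0.10 × 0.4 = 14.4, and SH+ 360 × 0.10 × 0.58 = 20.9. About 21 events against 14 are recorded although the true risks are equal.

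When only identically obtained information enters the between-arm table, f = 0 and the ratio is 1.00.

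**Step 3. Capture and reporting wording side by side**

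The capture sentence covers spontaneous reports and observed events. The reporting sentence names only events found through spontaneous reporting. Read strictly, observed events are recorded but drop out of the by-arm summary. Read broadly, they enter it with a route that EUC lacks. The section does not say which is meant.

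**The case against.** The strongest reply has four parts.

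**The summary is descriptive.** No test, effect estimate or comparative safety claim is planned, and individual events go to the steering committee within 24 h. That is correct, and a reader who infers a planned formal comparison of harms goes beyond the text. But a table by arm invites comparison, and leaving out a test does not equalize detection.

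**EUC is also observed.** Staff observation and assessments reach both arms; supervisors document participant distress during fieldwork {18a}; use of other mental health services is asked about at all follow-ups {11d}. This stands: EUC capture is lower, not absent. On the strict reading of the summary sentence, facilitator-observed events do not enter the table, which weakens the mechanism. It does not remove it, because SH+ mothers still have more occasions to volunteer a report.

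**The table is not the only evidence on harm.** A reader might infer that it is, or that deterioration under EUC would go unseen. The documents do not support either reading: K6, PHQ-9 and other symptom scales are measured at T0, T1 and T2 in both arms by blinded enumerators. What they do not give, as planned, is a harms summary, since they are analysed as continuous scores and a mean can improve while a minority worsens.

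**Contact counts are not a measure of bias.** A reader might count 5 + 2 = 7 in-person contacts against 2, a ratio of 3.5, or 10 against 5 with the calls, a ratio of 2. That treats a group session, an interview and an administrative call as equal detectors, and assumes full attendance and detection that simply adds up. The article supports none of this. Sessions also span five weeks, while follow-up runs to 12 months afterwards, so the extra detection may be small.

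The article also says openly that capture is non-systematic and gives low risk as the reason. That justifies light monitoring, but not monitoring that differs between arms.

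**Conclusion.** The point holds as a weakness of the harms summary. Following the plan as written gives a by-arm table with unequal ascertainment, likely to show relatively more events under SH+ when true risks are equal. The direction follows from the design; the size is unknown. The range of 1.07 to 3.0 rests entirely on assumed detection probabilities, on independent detection through the two routes, and on observed or session-prompted reports reaching the table. The lower end is close to no distortion. The mismatch between what is captured and what is summarized is a separate drafting fault that needs no assumption. The primary efficacy test on K6 is not affected.

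**What to change.** 1. **Reconcile section {22}.** State whether the by-arm summary covers all captured events or only spontaneous reports, and record the route of detection for each event.
2. **Use data already collected.** Tabulate by arm the proportion of mothers who worsen from T0 to T1 and from T0 to T2 on K6 and on PHQ-9, with a threshold fixed in advance. This needs no new data.
3. **Consider a minor amendment.** Add one short standard adverse-event question set, asked identically in both arms by the blinded enumerators at the remaining follow-ups. Ask it last, and word it so that it does not draw mention of SH+ sessions.
4. **Separate the sources.** Base any between-arm harms statement on items 2 and 3. List events detected in SH+ sessions on their own, and state that they have no EUC counterpart.

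The cost is a few added questions, one extra table and a small risk of unblinding enumerators, which the placing and wording in item 3 keep low. The trial status section reports SH+ delivery as ongoing and final follow-up as expected to be completed in February 2027, so an amendment could still take effect, at least for T2.

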### Criteria for discontinuing or modifying allocated interventions {11b}

Participants are free to withdraw from the study interventions at any time upon their request without providing a reason. The intervention facilitators or the clinical supervisor may also recommend withdrawal for a participant if they determine that continued participation is not in the participant’s best interest. Withdrawal will not affect access to any services or benefits available in the settlement.

Specific criteria for discontinuation from the intervention include the identification of imminent risk of suicide or harm to self/others, or the emergence of severe, acute psychiatric symptoms (e.g., psychosis or manic episodes) that require immediate, specialized care beyond the scope of this intervention. In such cases, the participant will be immediately referred to the appropriate mental health services within the settlement, and their participation in the intervention will be discontinued. Discontinuation from the intervention does not imply withdrawal from the study; where safe and consented, participants will be followed for outcome assessments in line with the intention-to-treat approach.

This protocol does not specify conditions for modifying the allocated interventions, as both the EUC and SH+ interventions are standardized and delivered according to a manualized protocol to ensure fidelity. No therapeutic content modifications are permitted; facilitators may make brief, culturally appropriate clarifications to enhance comprehension without altering core content or procedures. All instances of participant withdrawal or discontinuation from the intervention will be documented and any safety-related referrals will be reported in accordance with the trial’s adverse-event procedures.

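### The sentence on publishing harms names one of the two routes by which adverse events are captured, so events found by staff observation have no stated place in the by-arm summary

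*Protocol article*

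**What the plan says.** In the protocol article, section {22} describes capture as follows: "Adverse events will be captured non-systematically through spontaneous reporting and facilitator/staff observation". It expects that "clinically significant deterioration or safeguarding concerns may be identified during sessions or assessments".

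On handling inside the trial, the same section says "Any adverse event will be reported to the Trial Steering Committee within 24 h" and "Serious adverse events will be reported to the relevant ethics committees for review". Neither sentence distinguishes events by the way they were found.

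On publication, it says that "adverse events identified through spontaneous reporting will be summarized descriptively by trial arm", with two CONSORT reporting guidelines named as the standard.

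Section {11b} links to this. "Specific criteria for discontinuation from the intervention include the identification of imminent risk of suicide or harm to self/others"; the same sentence adds severe acute psychiatric symptoms. For such participants, "In such cases, the participant will be immediately referred to the appropriate mental health services within the settlement". The section requires every withdrawal or discontinuation to be documented, and "any safety-related referrals will be reported in accordance with the trial’s adverse-event procedures".

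**The concern.** The rule for publishing harms is narrower than the rule for capturing them. Two routes feed the record, and the sentence that governs the trial report mentions one. This is more than detail left to a fuller document: the article states a reporting rule, and that rule does not match the capture rule stated earlier in the same section.

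The gap touches events that the protocol itself foresees. A facilitator, supervisor or enumerator may be the one to notice that a mother is deteriorating or at risk, and {11b} gives facilitators and the clinical supervisor a part in recommending withdrawal. If such an event is classed as observed and not as spontaneously reported, the article does not say that a reader of the results will see it.

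The by-arm summary is the only public harms output to which {22} commits. No separate data monitoring committee is planned (section {21a}), and the Trial Steering Committee consists of the co-authors (section {5d}). If the wording stays open, whether observed events enter the table could be decided after their distribution by arm is known.

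**Working it through.** No arithmetic applies. The documents give no adverse-event rate or count, and the point depends on no sample size, effect size or error rate. The check is a comparison of sentences.

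1. **Capture ({22}).** Two routes are joined by *and*: spontaneous reporting, and observation by facilitators or staff. The umbrella term for both is *non-systematic*.

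2. **Internal reporting ({22}).** Any adverse event goes to the Trial Steering Committee within 24 h. Serious events go to the ethics committees. Both routes are covered.

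3. **Publication ({22}).** The by-arm descriptive summary is tied to events found by spontaneous reporting. That is the name of one item of the pair in step 1, not the umbrella term. The article does not say elsewhere that observed events will be published.

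4. **Link from {11b}.** The listed safety grounds for discontinuation lead to immediate referral, so each such case is also a safety-related referral. Safety-related referrals are reported under the adverse-event procedures. Those procedures are the ones in {22}, and they end in the sentence of step 3.

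Set side by side:

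| Event | Documented or reported internally | Stated place in the published by-arm summary |
|---|---|---|
| Spontaneously reported | Yes ({22}) | Yes ({22}) |
| Found by facilitator or staff observation | Yes ({22}) | None stated |
| {11b} safety discontinuation with referral, disclosed by the mother herself | Yes ({11b}, {22}) | Yes, if counted as a spontaneous report |
| {11b} safety discontinuation with referral, noticed by staff | Yes ({11b}, {22}) | None stated |

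5. **Why the route matters for comparing arms.** Both arms meet research staff at the enhanced usual care session and at the assessments. Only the SH+ arm also attends five weekly facilitated sessions of about 2 h each, or about 5 × 2 = 10 h of further contact. Section {13} places the single enhanced usual care session before randomization, so after allocation the control arm has no further intervention sessions from which to be discontinued. Observed events and discontinuations can therefore be expected to fall more in the SH+ column for reasons of contact alone.

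**The case against.** The strongest reply is that the sentence contains no word of exclusion. The capture sentence groups both routes as non-systematic, and *spontaneous reporting* may be shorthand for that whole stream. A facilitator who passes on what she saw could be said to have reported it spontaneously. This reading is possible and cannot be ruled out. It is the less natural one, because a few lines earlier the same phrase is one of two separate items. Even if it is what was meant, the text allows two different harms tables.

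A reader might go further and infer that suicide-risk and psychosis cases will be dropped from the reported harms. The documents do not support that. They do not exclude observed events. A mother may disclose suicidal thoughts herself, and that counts on either reading. Section {11b} has all discontinuations documented and safety-related referrals passed through the adverse-event procedures, while {22} sends every event to the Trial Steering Committee and serious ones to the ethics committees. The cases stay within safety reporting; what is unsettled is whether those found by observation reach the published summary.

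Other routes to outside scrutiny exist: audit by the research ethics committee (section {23}) and planned release of participant-level data (section {31c}). They soften the consequence but do not close the gap, since the article does not say that adverse-event records are part of the released data.

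It is also fair to say that a detailed listing by source goes beyond what an article must fix, and that the article does not say the source of each event is recorded. That part of the remedy is a preference.

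**Conclusion.** The point holds as a mismatch within section {22}, carried into {11b}. The publication sentence covers one of two capture routes, so events identified by observation, including safety-related discontinuations and referrals found that way, have no stated place in the by-arm harms summary.

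The conclusion rests on reading *spontaneous reporting* in the publication sentence with the meaning it has in the capture sentence. On the looser reading nothing would be left out, but the wording would still need to say so. The number of events affected cannot be estimated from the documents. No efficacy test or estimate is affected. The correction is worth making because it concerns the completeness of the harms comparison and is cheap. According to the trial status section, SH+ delivery was still under way and final follow-up was expected in February 2027, so the rule can be settled before results are known.

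**What to change.** Reword the publication sentence in {22} along these lines: *All adverse events captured by either route, together with safety-related discontinuations and referrals under section {11b}, will be summarized descriptively by trial arm.* The existing reference to the reporting guidelines can stay.

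Preferably add that the summary shows how each event was identified, by spontaneous report or by staff observation, and notes that only the SH+ arm has facilitator contact. This lets a reader separate a difference in harm from a difference in opportunity to observe it.

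Cost: one sentence and no new capture of events, since {22} already has all events reported and {11b} already has discontinuations documented. Showing the route may need one extra field on the event form. The downside is that the SH+ column may look less favourable because that arm is observed more closely; the split by route makes this visible.
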